#### Patient-reported outcome measures

A range of outcome measures will be used with participants with aphasia covering mood, wellbeing, activities, and communication and social participation. Measures chosen have either been developed specifically for neurologically impaired populations, some including people with aphasia or have been previously used with people with aphasia with good evidence of accessibility and acceptability. Where appropriate, the presentation of measures will be modified to make them aphasia-friendly in line with best practice guidelines [48]. The content, however, will not be changed to avoid affecting measures’ psychometric properties.

The following primary outcomes for participants with aphasia will be completed at baseline, 4 and 10 months post-randomisation: General Health Questionnaire-12 (GHQ-12) [32], using 0 0 1 1 scoring and the Depression Intensity Scale Circles (DISCS) [30]. The DISCS is being measured because some participants may not be able to complete the GHQ-12. This feasibility study will assess how often this is the case. The DISCS will be treated as the primary outcome measure only if there is ≥ 10% missing data in the GHQ-12 due to severity of aphasia; otherwise, DISCS will be a secondary outcome measure.

The following secondary outcomes for participants with aphasia will be taken at the same time points: Short Warwick Edinburgh Mental Well-being Scale-7 [49], Communicative Participation Item Bank [50], Community Integration Questionnaire—Adapted [51]. Proportion with high emotional distress vs low emotional distress as measured using the GHQ-12 (high distress = score of 3 or more, low distress = score of 0–2). There are additional psychological constructs that may be affected by peer befriending; however, the evidence base is not strong on whether existing measures on these constructs are responsive to change when used with people with aphasia. We will include two exploratory self-report outcomes for participants with aphasia in this study, the Communication Confidence Rating Scale for people with aphasia [52, 53] and the Friendship Scale [54] in order to see whether they may be suitable to use as secondary outcome measures in a definitive trial. These will be completed by participants with aphasia at each of the three time points.

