#### Outcome measures’ analyses

Despite the feasibility nature of the trial, we will compare the PEER and USUAL groups. These will be considered strictly exploratory. For primary outcome analysis, the comparison will be between the PEER and USUAL groups. The GHQ-12 will be scored 0 0 1 1 and summed, resulting in a 0–12 score range. This overall total GHQ-12 score will be analysed using linear mixed models with the 4 and 10 months post-randomisation measures as dependent variables, with a random intercept for individuals, and time, the baseline GHQ-12 score, a dummy variable indicating treatment group, the minimisation stratification factors, and any baseline variables that were imbalanced or that predicted missingness as independent variables to improve the plausibility of the missing at random assumption. A treatment group by time interaction term will be included to allow for extracting comparisons at the 4- and 10-month post-randomisation time points. These models will account for missing data using the maximum likelihood algorithm.

In addition, if at least some peer befrienders see multiple participants (e.g. > 2), we will explore the possibility of calculating the GHQ-12 intra-class correlation coefficient (ICC) by fitting a linear mixed effects model using the data from the PEER group with the 4 and 10 months post-randomisation measures as dependent variables and a random intercept for befriender to calculate the within-peer, between-peer, and total variability for clusters of participants seen by the same peer befriender. This ICC will help inform a sample size calculation for a larger trial and provide estimates of a peer befriender ICC to publish in the literature. If the DISCS is used as the main primary outcome instead of GHQ-12, it will be analysed in a similar manner.

The significant other outcomes and the secondary and exploratory participant with aphasia outcomes will be analysed in a similar manner to the primary outcome, comparing the outcomes between the PEER and USUAL groups. The peer befriender outcomes will be compared between the baseline and post-befriending time points using a paired t-test.

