All analyses will initially be conducted on an intention-to-treat basis. A second per protocol analysis will be done on the primary and secondary outcomes, excluding participants who are not in compliance with the protocol. Participants deemed not compliant will include those who did not consent at the second stage, completed less than six peer befriending sessions, were found to be ineligible after randomisation based on the inclusion/exclusion criteria, and participants in the usual care group who received peer befriending outside the study as reported to assessors or measured using the CSRI (in addition to their removal, we may explore analysing them in the peer group).

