#### Missing data

The amount and reasons for missing data will be summarised overall and by treatment group. Missing data will be accounted for where mixed models are applied under the missing at random assumption using the maximum likelihood algorithm. The baseline characteristics of those missing follow-up and those with complete follow-up will be summarised and variables affecting missingness will be examined using a logistic predictor of missingness model. This will be done by generating a binary variable for missingness for the primary outcome variable 10 months post-randomisation (we will explore the need to do this either separately or combined for the primary and secondary outcomes) and regressing this on baseline variables. Any variables found to be important predictors of missingness will be included in the primary and secondary outcome models. From a health economic perspective, where there is missing data, we will analyse the data on a complete case analysis basis and additionally use mean imputation for missing values. This will allow for a sensitivity analysis indicating whether missing values could be biasing the data.

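### Maximum likelihood in the primary mixed model does not cover a missing baseline GHQ-12, so a standard fit drops randomised participants who have usable follow-up

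*Protocol article*

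**What the plan says.** Under Outcome measures' analyses, the protocol article analyses GHQ-12 by "linear mixed models with the 4 and 10 months post-randomisation measures as dependent variables", with a random intercept per participant. The independent variables include "the baseline GHQ-12 score, a dummy variable indicating treatment group, the minimisation stratification factors", as well as time, a group-by-time interaction and any baseline variables found to be imbalanced or to predict missingness. Baseline GHQ-12 is thus a covariate and not one of the modelled outcomes.

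The same section says "These models will account for missing data using the maximum likelihood algorithm". The Missing data section repeats this without limiting it to outcomes: "Missing data will be accounted for where mixed models are applied under the missing at random assumption using the maximum likelihood algorithm". Its missingness model is built by "generating a binary variable for missingness for the primary outcome variable 10 months post-randomisation", so it does not look at missing baseline scores. On the analysis population the article says "All analyses will initially be conducted on an intention-to-treat basis".

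Under Patient-reported outcome measures, the article explains: "The DISCS is being measured because some participants may not be able to complete the GHQ-12". DISCS replaces GHQ-12 as primary outcome if 10% or more of GHQ-12 data are missing because of aphasia severity. The time point for that threshold is not given. Secondary, exploratory and significant-other outcomes are to be analysed in the same way as the primary outcome.

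**The concern.** The likelihood of this model is conditional on its covariates. If a 4- or 10-month score is missing, the other one still contributes, and the analysis is valid under missing at random. If the baseline score is missing, the model has no term for its distribution, and standard software removes the participant, including any observed follow-up scores. The unqualified missing-data statement therefore promises more than the specified model delivers.

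The trigger is foreseeable. The article itself expects that "some participants may not be able to complete the GHQ-12". Distress at entry is judged on DISCS (Participants with aphasia), and the Randomisation section does not require a scorable GHQ-12. A person can therefore be randomised without a baseline score and complete the questionnaire at 4 or 10 months.

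Such people are likely to have more severe aphasia, the group for whom the trial most needs to show that its measures and analysis work. According to the Discussion, effect sizes with 95% confidence intervals will help decide whether a definitive trial is worth planning, and that trial may well inherit this model.

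**Working it through.** **1. The plan's own figure.** Inputs from Sample size: 50 retained (25 per arm), two-sided alpha 0.05, effect 0.8 SD, SD about 3.6.
- Power = Φ(0.8 × √(25/2) − 1.96) = Φ(2.828 − 1.96) = Φ(0.868) = 0.807. With the t distribution it is 0.791. The stated 80% is reproduced.
- 0.8 × 3.6 = 2.88, the plan's approximate 3 points.
- 60 × 0.85 = 51, which agrees with at least 50 completing.

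**2. The mechanism.** In a simulated data set, 60 participants all had at least one follow-up score (111 follow-up rows) and 5 baseline scores were set to missing.

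| Model, fitted by maximum likelihood | Participants used | Follow-up rows used |
|---|---|---|
| Baseline as covariate, as written | 55 | 102 |
| Baseline as covariate, missing values set to the overall mean | 60 | 111 |

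If baseline is moved into the outcome vector, all 60 again contribute.

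**3. How many could be affected.** The document gives no rate of missing baseline GHQ-12, so this is a bound.
- 10% of 60 is 6. If the threshold is read at baseline, 6 missing because of aphasia would already make DISCS primary.
- While GHQ-12 stays primary, the most is therefore 5 of 60 (8.3%) for that reason.
- Missingness for other reasons is not capped. If the threshold is read at another time point, this bound does not apply to baseline.
- Only those with a missing baseline and at least one follow-up score are lost needlessly. Someone who never completes the GHQ-12 adds no follow-up outcome to any of these models.

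**4. Size of the loss.** Assume, as the worst case, that all 5 are among the 50 retained, leaving 45 (22.5 per arm).
- Confidence interval width: √(50/45) = 1.054, about 5% wider.
- Power = Φ(0.8 × √(22.5/2) − 1.96) = Φ(2.683 − 1.96) = Φ(0.723) = 0.765 (t: 0.746).
- The effect detectable with 80% power (t) rises from 0.81 to 0.86 SD.
- At 5% missing (2.5 of 50 on average), power is 0.787 (t: 0.770).

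**The case against.** The strongest reply is that handling of a missing baseline covariate is usually settled in the analysis plan, which is not shown, and that the article condenses a fuller protocol. Nothing in the article says that such participants are excluded, and imputing the baseline would be compatible with every sentence in it. This stands in part: exclusion is the default of a standard fit, not a written rule. But the article does not merely stay silent. It fixes the outcomes, the covariates and the missing-data method, and asserts that the method accounts for missing data. That assertion can be corrected on its face. The only imputation it names belongs to the health economic analysis.

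A reader might also infer several stronger things, which the document does not support:
- **Bias between arms.** Randomisation follows completion of the baseline assessments, so a missing baseline score cannot depend on allocation. Excluding on a pre-randomisation variable still leaves a randomised comparison, and aphasia severity is adjusted for as a minimisation factor.
- **A planning SD from a milder group.** Descriptive statistics takes sample-size inputs from summary statistics for the whole trial population at each time point, not from this model.
- **A silent loss.** The Missing data section reports the amount of and reasons for missing data, overall and by group.
- **Loss of severe aphasia only.** Baseline scores may be missing for other reasons. Aphasia-friendly presentation and additional assessment visits should keep the number down.

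It is also fair that intention to treat is set there against a per-protocol analysis based on compliance, and that the group comparisons are labelled exploratory, with feasibility outcomes taking precedence. Both points lower the stakes, but neither makes the missing-data statement correct.

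**Conclusion.** The point holds in a limited form. As specified, maximum likelihood covers missing 4- and 10-month scores only. A standard fit would drop a randomised participant with no baseline GHQ-12 even when both follow-up scores are present, which does not sit with the missing-data and intention-to-treat statements.

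The effect is modest: at worst about 5% on the confidence interval and about 4 percentage points of power, plus under-representation of severe aphasia in an exploratory estimate. These figures assume that GHQ-12 stays primary, that the 10% threshold is read at baseline, that aphasia is the only reason for missing baselines, and that everyone affected has usable follow-up. If fewer have follow-up, the loss is smaller; if other reasons add to it, larger. The 10% switch does not protect the secondary, exploratory and significant-other outcomes, which share the same model form. It is worth correcting because the correction costs little.

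**What to change.** Limit the maximum likelihood statement, in both places, to missing outcome data. Then state how a participant with a missing baseline score is kept, by one of two routes:

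- **Single imputation of the baseline covariate without regard to arm**, for example the overall mean, with or without a missing indicator. This leaves the model otherwise unchanged.
- **Joint modelling of baseline, 4 and 10 months**, with a common baseline mean for both arms, arm effects at 4 and 10 months, and the minimisation factors retained. Use an unstructured covariance. A random intercept alone would force equal variance and correlation across all three times, which is doubtful when entry is restricted to low distress.

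Apply the same rule to the secondary, exploratory and significant-other outcomes, and to any further baseline covariate added because of imbalance or prediction of missingness, since an incomplete one causes the same loss.

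The cost is a little more analysis work and no new data. The joint model with three time points has 6 covariance parameters (3 × 4 / 2), against 2 for a random intercept with residual variance. With about 50 participants, imputation is the simpler choice.

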### Intervention

#### Intervention arm—usual care + peer befriending (PEER)

Participants in the intervention arm will receive all usual care available in their borough and peer befriending. Peer befriending aims to utilise the skills, knowledge, and ‘lived experience’ of people with longer-term aphasia to offer emotional, social, and informational support to others with aphasia. It aims to help people move forward and develop their own strategies for adjusting to life post-stroke. In the trial, peer befriending is offered at a time of transition (discharge from hospital and withdrawal of intensive therapeutic input) and increased need. The intervention is described according to the TIDieR checklist [28] (see Additional files 2).

Peer-befrienders will receive training based on a study-adapted version of a peer befriending intervention manual [42] and ongoing supervision and support. The training will last 5–6 h across 2–3 days to accommodate the needs of the participants in the group (e.g. levels of attention and fatigue). The training will be conducted by two facilitators, who both have experience of communicating with people with aphasia. One of the trainers has additional experience of running peer befriending schemes. The training will cover a range of topics related to peer befriending (e.g. the role of a befriender, hopes and fears, how to have a conversation as a befriender, setting objectives, identifying barriers, dealing with challenging situations), health and safety, and dealing with adverse events. Peer befrienders will receive a copy of a peer befriender handbook, which contains key information from the manual in aphasia-accessible format. It is anticipated that each peer-befriender will work with 2–4 participants during the trial and no more than two at any one time.

Peer-befrienders will be offered monthly group supervision sessions. These sessions will be conducted by a single befriender facilitator (also involved in the training) who is a trained SLT with extensive experience in working with people with aphasia. The sessions will be an opportunity to share experiences and discuss any difficulties that have arisen. Peer-befrienders who are facing particular challenges will receive supplementary individual supervision and support from the same befriender facilitator. Peer befrienders and the facilitator will record these challenges. The facilitator will keep detailed written notes to summarise the content of each supervision session.

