### Sample size

We will recruit in total 60 participants with aphasia (30 in each arm of the study). Allowing for a ~ 15% lost to follow-up rate, at least 50 will complete the study. With 60 participants recruited, we will be able to estimate a 95% confidence interval for the recruitment rate to within approximately 25%. This sample size will be adequate to estimate important parameters needed to inform the design and the sample size of a full trial, such as the standard deviation, consent rates, event rates. This sample size also meets recommended sample sizes for feasibility studies [59].

Although this is a feasibility study, we would like to estimate exploratory differences between the PEER and USUAL arms. If we assume we retain 50 participants at follow-up, a two-sided test, *α* = 0.05, and independence of participants, we will have 80% power to detect an effect size of approximately 0.8. The standard deviation of the primary GHQ-12 outcome in a generic population of patients with stroke has been shown to be approximately 3.6—this was using the 0 0 1 1 scoring, with total scores ranging from 0 to 12 [60]. This effect size corresponds to an approximate mean difference of 3 points between groups. This sample size is sufficient for these exploratory comparisons; however, in a definitive trial, we would want to have higher power to detect a smaller effect size. This feasibility study will give us a standard deviation specific to the group that we would be interested in recruiting for a definitive trial, so would help to inform such a sample size calculation.

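### The befriender ICC model pools two GHQ-12 scores per person but names no participant effect, so the ICC would be biased upward

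*Protocol article*

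**What the plan says.** All references are to the protocol article.

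- **Main GHQ-12 model (Outcome measures' analyses).** The 4- and 10-month scores are modelled jointly, "with a random intercept for individuals, and time, the baseline GHQ-12 score", plus treatment group and other covariates. It has no befriender term.
- **ICC model (same section, next paragraph).** If some befrienders see several participants (the example given is more than two), the team will explore estimating a GHQ-12 ICC. The data are the PEER group's 4- and 10-month scores, and the random part is "a random intercept for befriender to calculate the within-peer, between-peer, and total variability for clusters of participants seen by the same peer befriender". No participant term is named. The stated uses of the ICC are the sample size of a larger trial and publication.
- **Caseload (Intervention arm).** It is anticipated that "each peer-befriender will work with 2–4 participants during the trial".
- **Sample size.** Power for the group comparison assumes "independence of participants, we will have 80% power to detect an effect size of approximately 0.8".

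**The concern.** Each PEER participant contributes two scores to the ICC model. Those scores resemble each other because they come from one person, whoever the befriender is. The main model allows for this through its individual intercept. The ICC model splits variability into only two parts, within and between befrienders, so part of the person-level similarity is attributed to the befriender.

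The ICC is a design parameter. If it is too high, the definitive trial's design effect is too large, and others who use the published value inherit the error.

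The between-arm model raises a related but smaller question. If befrienders do induce clustering, a model with no befriender term gives a PEER–USUAL confidence interval that is somewhat too narrow.

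**Working it through.** **Inputs from the document.** 30 participants per arm; 50 retained (25 per arm); two-sided alpha 0.05; effect size 0.8; SD 3.6; m = 2 to 4 participants per befriender; two follow-up scores per person. Thirty PEER participants at 2 to 4 each imply 30/4 = 7.5 to 30/2 = 15 befrienders, so about 8 to 15.

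**Assumed, because the document gives no value.** rho = var_p/(var_b + var_p + var_e) = 0.3, 0.5 or 0.7, where b, p and e stand for befriender, participant and residual. Befriender ICC = 0.02 to 0.10 for the between-arm check.

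**1. The plan's own figure.** With 25 per arm and d = 0.8, power is 80.7% (normal approximation) or 79.1% (t). 0.8 × 3.6 = 2.88, about 3 points. 60 × 0.85 = 51, so at least 50. The stated power reproduces under independence.

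**2. Bias of the ICC as written.** Take a balanced layout with m participants per befriender and two scores each.
- Expected mean square between befrienders: var_e + 2 var_p + 2m var_b.
- Expected pooled mean square within befrienders: [(m-1)(var_e + 2 var_p) + m var_e]/(2m-1) = var_e + 2(m-1) var_p/(2m-1).
- The difference divided by 2m is var_b + var_p/(2m-1).

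The two estimated components still sum to the true total, so the ICC is raised by rho/(2m-1).

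| m | divisor 2m-1 | rho 0.3 | rho 0.5 | rho 0.7 |
|---|---|---|---|---|
| 2 | 3 | +0.10 | +0.17 | +0.23 |
| 3 | 5 | +0.06 | +0.10 | +0.14 |
| 4 | 7 | +0.04 | +0.07 | +0.10 |

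**3. Simulation check (10 befrienders × 3 participants, rho = 0.5, 20,000 trials).** Untruncated values are ratios of mean variance components. Truncated values set negative befriender variances to zero and are averaged over trials.

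| True ICC | As written, untruncated | As written, truncated | With participant effect, untruncated | With participant effect, truncated |
|---|---|---|---|---|
| 0 | 0.10 | 0.11 | 0.00 | 0.055 |
| 0.05 | 0.15 | 0.15 | 0.05 | 0.085 |

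The participant effect removes the bias derived in step 2. It does not remove the smaller bias caused by truncation.

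**4. Precision of the correct ICC.** With a true ICC of 0 and rho of 0.3 to 0.7, the simulated standard error (40,000 trials per setting) is 0.17 to 0.21 for 15 × 2, 0.12 to 0.15 for 10 × 3 (0.14 at rho = 0.6) and 0.10 to 0.12 for 8 × 4. The befriender variance comes out at or below zero in about half of these trials.

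**5. Consequence for the definitive trial.** Suppose the true ICC is 0, the caseload is unchanged and allocation is 1:1. The false PEER-arm design effect is 1 + (m-1) × bias. At m = 3 and rho = 0.5 it is 1 + 2 × 0.10 = 1.20, and the total sample is inflated by (1 + 1.20)/2 = 1.10, or 10%. Over rho 0.3 to 0.7 at m = 3 the design effect is 1.12 to 1.28 and the excess 6% to 14%.

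**6. Between-arm model.** If clustering exists in the PEER arm only, the true SE divided by the nominal SE is sqrt[(2 + (m-1) ICC)/2]. At m = 2 and ICC 0.02 this is sqrt(2.02/2) = 1.005; at m = 4 and ICC 0.10 it is sqrt(2.30/2) = 1.072. Actual alpha is then 0.051 to 0.068. Power, once clustering is allowed for, is 80.4% to 75.1%, against 80.7% under independence.

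**The case against.** - **The sentence may be shorthand.** The ICC step is conditional and tentative, it lists no covariates, and the article condenses a fuller protocol. Fitting each time point separately would avoid the bias. This lowers certainty about what will be done. However, the text does name the outcomes and the random term, and its wording on the two time points matches the joint main model one paragraph earlier, where the individual intercept is named. A clarification is needed on either reading.
- **The size is assumed.** This stands. No rho is given, and adjusting for baseline GHQ-12 would probably lower it. The largest biases belong to m = 2, whereas the step is meant for the case where some befrienders see more than two people, so m = 3 to 4 or a mixture is more relevant.
- **A positive ICC would not be due to the missing term alone.** This also stands. A reader might infer that the corrected model would report zero when befrienders have no effect. Truncation at zero with so few befrienders leaves an average near 0.06 at 10 × 3.
- **The error is conservative.** It makes a future trial larger, not underpowered. That limits the harm but does not make the published figure right.
- **The group comparison is exploratory.** A reader might infer that the power statement is wrong or that the main model must be replaced. The document supports neither. Independence is declared as an assumption, the arithmetic reproduces, the comparisons are labelled strictly exploratory, and the protocol recognises clustering through the ICC step itself.

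**Conclusion.** The point holds for the ICC model. As written, it would give an ICC too high by about rho/(2m-1): +0.06 to +0.14 at m = 3, +0.04 to +0.10 at m = 4 and +0.10 to +0.23 at m = 2. This rests on a joint fit of both time points, an assumed rho of 0.3 to 0.7 and roughly equal caseloads. The direction needs only a positive correlation between a person's two scores, which the main model already presumes.

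The between-arm omission is secondary. For assumed ICCs of 0.02 to 0.10, the SE is understated by about 0.5% to 7%, which supports a sensitivity analysis and no more.

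The point should be fixed, because the ICC is intended for planning and publication. No conclusion of this feasibility trial depends on it.

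**What to change.** 1. In the PEER-only ICC model, add a random intercept for participant nested within befriender, or state that the ICC will be estimated separately at 4 and at 10 months.
2. For the joint fit, define the ICC as befriender variance / (befriender + participant + residual variance).
3. Report it with a 95% CI, the number of befrienders and their caseloads, and say so if the befriender variance is estimated at zero. With a standard error of roughly 0.10 to 0.20, a point estimate alone should not be carried into a sample size calculation.
4. Add a sensitivity analysis of the PEER–USUAL comparison with a befriender random effect in the PEER arm only. Keep the present model as the main exploratory analysis.

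**Cost.** A few words of analysis text, one random term in the ICC model and one additional fit. No new data are needed. The sensitivity analysis will give a slightly wider CI if clustering is present, and with 8 to 15 befrienders its befriender variance may be estimated at zero.
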